## Abstract

**Background:**

The traditional Chinese theory of acupuncture emphasizes that the intensity of acupuncture must reach a threshold to generate *de qi* (a specific and compound sensation during the acupuncture), which is necessary to achieve the best therapeutic effect. However, the notion that *de qi* must be achieved for maximum benefit has not been confirmed by modern scientific evidence. This study aims to compare the efficacy of acupuncture with either strong (intended to elicit *de qi*) or weak stimulation among patients with allergic rhinitis.

**Methods/Design:**

This study compares real versus sham acupuncture in 140 patients with a history of persistent allergic rhinitis (PER) or intermittent allergic rhinitis (IAR) and with a positive skin prick test (SPT). The trial will be conducted in the Teaching Hospital of Chengdu University of Traditional Chinese Medicine (China). In the study, patients will be randomly assigned into two groups by computer-generated randomization and assessed prior to treatment. They will then receive 12 sessions of treatments for 4 consecutive weeks and have a follow-up phase lasting 12 weeks. The main outcome measures include the primary and secondary indicators. Primary indicators are subjective symptoms scores as evaluated by visual analogue scales (VAS), rhinoconjunctivitis quality of life questionnaires (RQLQ), and the Modified Massachusetts General Hospital acupuncture sensation scale, Chinese version (C-MMASS). The secondary indicators are the results of laboratory examinations, such as serum allergen-specific immunoglobulin E (sIgE) nasal inflammatory cells counts (mast cells, eosinophils, and T cells), and nitric oxide concentration in nasal excretion. The use of anti-allergic medication will also be recorded as one of the secondary indicators. Furthermore, adverse events will be recorded and analyzed. Intention-to-treat analysis (ITT) and per-protocol (PP) analysis will be performed to test and verify the results in this trial.

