### Outcome measurements

#### Primary outcomes

For the evaluation of the main outcome measures patients are requested to fill in a questionnaire including the Rhinitis Quality of Life Questionnaire (RQLQ) [18, 19], the visual analogue scale (VAS) [20] and C-MMASS (Massachusetts General Hospital Acupuncture Sensation Scale, modified Chinese version) [21].

In VAS, the severity of the combination of the nasal symptoms will be subjectively rated by the study patients on the scale. The severity of symptoms can be divided into mild, moderate, or severe based on the total severity VAS score (0 to 10 cm: mild, VAS 0 to 3; moderate, VAS 3.1 to 7; severe, VAS 7.1 to 10). VAS scores will be recorded every two weeks throughout the whole trial.

The RQLQ (see Additional file 1) evaluates impairment of everyday life (activity, sleep, everyday life problems, condition of health) caused by symptoms of the eyes and nose. It contains 28 questions related to these dimensions. Each question can be divided into seven degrees: 0 - not trouble, 1 - any trouble at all, 2 - somewhat troubled, 3 - moderately troubled, 4 - quite a bit of trouble, 5 - very troubled, 6 - extremely troubled. It will be measured by questionnaire at baseline, at the end of treatment, during the follow-up period, and at the end of the follow-up period (a total of five times). Both the scores of VAS and RQLQ questionnaire will be blindly assessed.

C-MMASS (see Additional file 2) is an accepted method of objectively scoring the sensation of *de qi*. Immediately after removing the needles during the 1st, 3rd, 5th, 7th, 9^th^, and 12^th^ sessions, patients will be asked to fill in the questionnaire. Patients were questioned about whether each of the sensations of *de qi* had occurred during the session.

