### Statistical analysis

Analysis of all data in this trial will be performed by the National Clinical Trial Center of Chinese Medicine (Chengdu GCP Center) in China, which is performed in a blinded manner because analysis of data is done by a special analysis-researcher. The data will be analyzed with SPSS 18.0 and SAS 9.0 (SAS Institute Inc. [name]) statistical software packages. Results will be summarized as means, standard deviations, and 95% confidence intervals (CIs) for continuous data, medians, quartiles, and ranges for rank data, and frequencies and percentages for discrete data.

The first step of analysis is to check whether *de qi* groups were more efficacious in treating AR than the control group. If *de qi* treatment is more effective than the control group in treating AR, the next step is to make comparisons among *de qi* group in the relationship between the effectiveness of treating AR and the scores of the C-MMASS.

The intention-to-treat (ITT) group is defined as the patients who are randomized. The per-protocol (PP) group is defined as the patients who completed the study and do not have major protocol violations. All analyses were based on the ITT group and PP group. And the result of the ITT analysis will be compared with that of the PP analysis to check whether the results are consistent.

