## Discussion

The main objective of this trial is to investigate the relationship between the effect of the acupuncture for patients with AR and the needle sensation of *de qi*. This objective has two aspects: one is whether acupuncture with *de qi* is more efficient than without *de qi*; the other is the relationship between *de qi* and efficiency. In this trial, we assess the strength of *de qi* by the score of C-MMASS and the efficiency by the score of RQLQ. We want to know whether a high score equates to high efficiency or not. The result of this trial is expected to provide convincing evidence that strengthened stimulation during acupuncture for the treatment of allergic rhinitis is more effective.

In the literature, sham acupuncture is considered to be a placebo treatment in acupuncture studies. There are two common types of sham control for the clinical study for acupuncture, one is a technique in which needles are inserted shallowly at defined acupoints, another is at locations of 1 to 2 cm away from the defined acupoints. In our study we chose to use the point superficial needle-insertion method. The needles are inserted into the sham points to a depth of 3 mm and are retained at the subcutaneous level. To ensure the efficacy and safety of the treatment, acupuncturists should undergo special training in Teaching Hospital of Chengdu University of Traditional Chinese Medicine and have sufficient knowledge, special technique, and good experience in acupuncture.

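### Three scores are primary with no deciding outcome, visit or rule for the efficacy step, and C-MMASS is wrongly labelled as one of them

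*Protocol article*

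**What the plan says.** - **Abstract, Methods/Design:** "Primary indicators are subjective symptoms scores as evaluated by visual analogue scales (VAS), rhinoconjunctivitis quality of life questionnaires (RQLQ), and the Modified Massachusetts"; the third is the needle-sensation scale, C-MMASS. All three carry equal status.
- **Primary outcomes:** the same three are introduced with "For the evaluation of the main outcome measures patients are requested to fill in a questionnaire including the Rhinitis Quality of Life Questionnaire (RQLQ"), then VAS and C-MMASS. No order, key visit or any/all rule follows.
- **Timing:** for VAS, "VAS scores will be recorded every two weeks throughout the whole trial"; Table 2 shows week 0 and weeks 2 to 16. RQLQ is collected at baseline and at four later visits, the last "at the end of the follow-up period (a total of five times"). C-MMASS is completed at six sessions: "Immediately after removing the needles during the 1st, 3rd, 5th, 7th", then the 9th and 12th.
- **What C-MMASS measures:** it "is an accepted method of objectively scoring the sensation of" de qi.
- **Interventions:** needles in the de qi arm are manipulated until de qi occurs and again to maintain it. Control needles go in 3 to 5 mm and are not manipulated.
- **Statistical analysis:** "The first step of analysis is to check whether *de qi* groups were more efficacious in treating AR than the control group". Only if the answer is yes does the second step relate effectiveness to C-MMASS within the de qi group.
- **Discussion:** "we assess the strength of *de qi* by the score of C-MMASS and the efficiency by the score of RQLQ".

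**The concern.** Step 1 carries the headline claim and decides whether step 2 is done. Efficacy in treating rhinitis could be read from VAS, from RQLQ, from both or from either, at any visit between week 2 and week 16. The Discussion points to RQLQ, but the two places that define the primary outcomes do not give it precedence. A choice left open until results are seen does not hold the 5% error rate used in the sample size calculation.

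The C-MMASS label is a separate fault. A primary outcome should bear on whether patients improve. C-MMASS records whether the needling was felt as intended, and it is also the explanatory variable in step 2. It should not be reported as a primary result of treatment.

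**Working it through.** **The plan's own figure.** Sample size calculation gives 70 per group at two-sided 5% (z = 1.96), 90% power (z = 1.282) and 20% dropout. It defines two rates, π1 and π2, but gives no values and ties them to no outcome, so 70 can be neither reproduced nor refuted. It is attainable. With assumed rates of 30% and 60%, the pooled two-proportion formula gives

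n = [1.96·√(2·0.45·0.55) + 1.282·√(0.30·0.70 + 0.60·0.40)]² / 0.30² = (1.379 + 0.860)² / 0.09 = 55.7, so 56, and 56/0.8 = 70.

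None of the three primary scales is defined as a rate, so this section does not show which one decides.

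**Counting the comparisons (Table 2).** VAS after baseline: weeks 2, 4, 6, 8, 10, 12, 14, 16 = 8. RQLQ after baseline: weeks 4, 8, 12, 16 = 4. Total 12 clinical outcome-visits.

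**False-positive chance with no effect, each test two-sided 5%, any one sufficient.** If independent: two tests give 1 − 0.95² = 9.75%, and twelve give 1 − 0.95¹² = 46.0%. Repeated scores on the same patients are correlated, and the document gives no correlations. The other rows therefore use assumed values, with 200,000 simulated multivariate normal draws each.

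| Assumed correlation (within scale / between scales) | VAS or RQLQ, one visit | Any of 4 RQLQ visits | Any of 12 | Any of 12, in favour of de qi |
|---|---|---|---|---|
| Independent | 9.75% | 18.5% | 46.0% | 26.2% |
| 0.5 / 0.3 | 9.6% | 15.7% | 35.3% | 17.7% |
| 0.7 / 0.5 | 9.1% | 13.0% | 26.4% | 13.2% |
| 0.9 / 0.7 | 8.3% | 9.3% | 16.7% | 8.4% |

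The independent entry in the last column is 1 − 0.975¹². With one prespecified test the corresponding figures are 5% in either direction and 2.5% in favour of de qi. Correlations of 0.3 / 0.3 give 39.5% for any of 12.

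**C-MMASS, sections side by side.** Primary outcomes says that it scores the sensation. Interventions makes the arms differ in whether that sensation is produced and maintained. Statistical analysis and the Discussion use it as the strength of de qi, to be related to effectiveness. These three uses agree with one another; the primary label does not fit them.

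**One primary test at the existing size.** Evaluable per arm: 70 × 0.8 = 56. Standardised difference detectable with 90% power: (1.96 + 1.282)/√(56/2) = 3.242/5.292 = 0.61.

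**Keeping two clinical primaries instead.** At 2.5% each (Bonferroni), power at that difference is 84%. Restoring 90% needs 67 evaluable, and 67/0.8 gives 84 randomised per arm.

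**The case against.** The multiplicity method, the repeated-measures model and test details are commonly left to an analysis plan, and that plan is not shown. Nothing in the article says that scores will be tested visit by visit or that one significant visit is enough, and the single 5% level is assigned to no outcome. This stands: the table is conditional, and its independent row is an upper reference, not the trial's error rate. It does not remove the point. Which outcome decides, and when, is protocol content. Here it is given as an unordered list of three, beside a Discussion that uses RQLQ. Taking the Discussion as the answer still leaves four visits.

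A reader might infer that C-MMASS could itself pass step 1, so that a positive primary result would be nearly certain without any clinical effect. The documents do not support this. Step 1 asks about efficacy in treating rhinitis, which C-MMASS does not measure, and both later mentions give it an explanatory role. The size would also be assumed, since no C-MMASS difference is stated. With 56 per arm and three independent tests, the chance of at least one significant primary is 42% at a standardised C-MMASS difference of 0.3, 78% at 0.5 and 99% at 0.8.

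A reader might also assume 90% power for VAS and RQLQ separately and work out the loss from requiring both. The sample size rests on two unnamed rates, so no power is stated for either score.

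**Conclusion.** The concern holds in this form. The article names three primary outcomes and no deciding score, visit or rule, while its efficacy step depends on one being chosen. Between VAS and RQLQ at one visit the false-positive chance is about 8–10% if either suffices. It is about 17–35% if any of the 12 outcome-visits suffices, under assumed within-scale correlations of 0.5 to 0.9 and between-scale correlations of 0.3 to 0.7 (46% if independent). Both ranges assume an either/any rule, which the text neither states nor excludes. The C-MMASS fault is one of classification: its primary label is wrong, but the document does not make it a route through step 1.

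**What to change.** By a dated amendment to protocol and registry:

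- Name one clinical primary outcome at one visit. RQLQ at week 4, the end of treatment, adjusted for its baseline value, agrees with the Discussion's use of RQLQ and is already scheduled. The choice of week is a proposal; the Discussion gives none.
- Make VAS and all later visits secondary, with VAS tested only if the primary test is significant.
- Reclassify C-MMASS as a manipulation check and as the exposure in step 2.
- State that step 1 is decided by the one primary test.
- Restate the sample-size basis for that outcome, keeping 70 per arm. The sponsor should say why a standardised difference of about 0.61 is plausible for RQLQ; the document gives neither a standard deviation nor a target difference.

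The amendment must precede unblinding. Because the article opens the code only after analysis of groups labelled A and B, it should also precede any comparison of A with B.

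No data collection changes. The costs are a new sample-size justification, one score carrying the claim, and an amendment made after the first randomisation (27 September 2013), which the report should disclose.

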**Discussion:**

The results of this trial will demonstrate the efficacy of using acupuncture to treat allergic rhinitis and verify whether the effectiveness of acupuncture is related to the needle sensation *de qi*.

**Trial registration:**

Chinese Clinical Trial Registry: ChiCTR-TRC-13003594 (registered on 16 August 2013, and the first patient was randomized on 27 September 2013).

**Electronic supplementary material:**

The online version of this article (doi:10.1186/1745-6215-15-301) contains supplementary material, which is available to authorized users.

## Background

Allergic rhinitis (AR) is a symptomatic disorder of the nose resulting from an immunoglobulin E (IgE) -mediated immunological reaction to allergen exposure. Its major symptoms include rhinorrhea, nasal itching, obstruction, and sneezing, all of which are reversible either spontaneously or with treatment [1]. AR has become a major health problem worldwide. It has been estimated by the ARIA (Allergic Rhinitis and its Impact on Asthma) 2008 document that over 600 million patients from all countries, in all ethnic groups, and of all ages suffer from AR [2]. It dramatically impacts quality of life (QOL) and creates a high economic burden. The conventional treatment of AR symptoms, such as nasal obstruction, rhinorrhea, sneezing, and itching, includes the use of intranasal corticosteroids, oral antihistamines with or without decongestants, immunotherapy, and education [3]. A remarkable number of patients with AR are not satisfied with conventional medical treatment for they repeatedly experience side effects and incur additional healthcare costs. As an available and affordable treatment choice, acupuncture has been accepted as a therapeutic option for relieving symptoms of AR in China and other countries [4–6].

However, studies on the efficacy of acupuncture in patients with AR have yielded inconclusive results. For example, Choi *et al*. [7] stated that active acupuncture showed a significantly greater effect on symptoms of allergic rhinitis than sham acupuncture, while Magnusson *et al*. [8] found that there were no differences in clinical symptoms which had been seen between active versus sham acupuncture. At the same time, a number of trials have the same situation in migraine [9, 10], low back pain [11, 12] and some other diseases. All of those trials did not find verum acupuncture more effective than sham acupuncture and did not emphasize that the verum acupuncture group must have the needle sensation of *de qi*.

*De qi* is an internal compound sensation of soreness, tingling, fullness, aching, coolness, warmth, heaviness, and a radiating sensation at and around acupoints, and is elicited by manipulation of the needles (rotated as well as being moved both upward and downward). According to the traditional theory and clinical practice, *de qi* is one of the fundamental characteristics of acupuncture. The importance of *de qi* was first mentioned *circa* 100 BC, in the Huangdi Neijing (The Yellow Emperor’s Classic of Internal Medicine). For example, Ling Shu (chapter 1) [13] reads, ‘For acupuncture to be successful, the qi must arrive (qi zhi). Acupuncture’s effects come about like the clouds blown away by the wind.’ Another example is in Ling Shu (chapter 9) where it is advised that ‘The acupuncturist should devote all his/her concentration to the needle, keep the needle on the surface and move it gently, until the qi has arrived (qi zhi).’ There is a long-held belief in the theory of acupuncture that the intensity of the stimulus must reach a certain threshold to elicit *de qi*, which plays a pivotal role in achieving the best therapeutic effects [14]. So far, more and more studies have begun to assess *de qi* by using different scales, and to investigate the relationship between *de qi* and the therapeutic effects [15, 16]. However, this long-held belief has not been confirmed by sufficient evidence from randomized controlled trials about AR.

As mentioned above, we have designed a randomized, double blind, large scale clinical trial to compare the efficacy of acupuncture with either strong (intended to elicit *de qi*) or weak stimulation among patients with AR. The design and methodologies of this study have been approved by the Sichuan Regional Ethics Review Committee on Traditional Chinese Medicine with an ethics approval number of 2013KL-025. The work reported in this article is registered with the Chinese Clinical Trial Registry (registration number: ChiCTR-TRC-13003594).

## Methods/Design

### Study design

This trial is a single center, double blind, sham group randomized controlled trial, which will be performed at the Department of Otorhinolaryngology, Head and Neck Surgery, Teaching Hospital of Chengdu University of Traditional Chinese Medicine, China. The study will be sequentially conducted as follows: a run-in period of 2 weeks prior to randomization, a treatment period of 4 weeks (3 sessions per week), and a follow-up period of 12 weeks. The total study period will be 18 weeks. At the end of the run-in period participants will be randomized to the active acupuncture group or the sham acupuncture group by a computer-generated random number list (Figure 1).

**Figure 1 Fig1:**
[figure not shown]
**Screening, recruitment, randomization, and participant follow-up schedule of the trial.** C-MMASS, Modified Chinese version of the Massachusetts General Hospital Acupuncture Sensation Scale; RQLQ, Rhinoconjunctivitis Quality of Life Questionnaires; VAS, Visual analog scales.

### Randomization and blinding

The randomization sequence will be computer generated by independent research staff using software called Statistical Program for Social Sciences (SPSS 18.0 IBM China Company headquarters, Beijing, China). After randomization, group assignments will be concealed in light-proof and sealed sequentially numbered envelopes. The included participants will be randomly enrolled by sealed envelope and assigned to the *de qi* group or sham-acupuncture control group in a ratio of 1:1. Then the person in charge of the envelopes will give the specified envelope to the acupuncturist. To preserve masking, only the acupuncturists will have access to the treatment allocation.

Randomization will be performed by researchers who are not in direct contact with the participants. Participants, researchers, and study physicians who interview and recruit patients are blinded to the group assignments. The acupuncture practitioners will be informed due to the nature of the intervention, but they will be asked not to communicate with the participants or assessors regarding treatment procedures and responses.

The two randomized groups will be named A or B in the medical records and the case report forms will not be directly linked to the treatment. All information will be locked out and saved in a database before statistical analysis is performed. After statistical analysis, the blind exposure will be provided.

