### Interventions

During the treatment process, all participants will be explained the meaning of acupuncture and *de qi* by the acupuncturists in the same way. Both the *de qi* and control group participants will receive acupuncture treatments respectively, 3 times a week for a total of 12 sessions over 4 weeks. The same number and type of needles (Hwato disposable sterile acupuncture needles Suzhou Medical Supplies Co., Ltd., Suzhou, China) will be used for both groups. The needle selected was 0.30 mm in diameter and the length of the needle selected varied according to the point location. Needle sites in both active and sham acupuncture groups will be swabbed with 75% alcohol before insertion. On withdrawal of the needle, dry sterilized cotton balls will be firmly applied to the insertion points. Medications which could affect the allergic rhinitis symptoms are not permitted.

In the *de qi* group, the needle was inserted transversely, obliquely, or perpendicularly depending on the acupoints selected with 10 to 30 mm in depth. The acupuncturist will manipulate the needles manually after insertion, using techniques such as lifting, thrusting, and twirling, until *de qi* was achieved. The needles will be left in place for 30 minutes. During the treatment session, the patient will be asked about *de qi* every 10 minutes and the needles will be manipulated to maintain the intensity of the sensation (Table 1). In the control group the needles will be inserted to a depth of 3 to 5 mm perpendicularly to the skin and left in place for 30 minutes without manipulation. Patients in the other treatment group are treated in different rooms. All sessions for each patient were performed by the same acupuncturist.

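### A shared A/B group letter in the medical records means that one recognised patient can reveal the arm of every patient whose record is seen; a unique number would limit this to one

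*Protocol article*

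**What the plan says.** All the key statements are in the protocol article.

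- **Label.** Under Randomization and blinding: "The two randomized groups will be named A or B in the medical records". The sentence goes on to say that "the case report forms will not be directly linked to the treatment". The label belongs to the group, so every patient in an arm has the same letter. Whether the letter also stands on the case report forms is unclear from the wording.
- **Who may know the arm.** The same section: "To preserve masking, only the acupuncturists will have access to the treatment allocation".
- **Who is blinded.** The same section: "Participants, researchers, and study physicians who interview and recruit patients are blinded to the group assignments". Under Primary outcomes: "Both the scores of VAS and RQLQ questionnaire will be blindly assessed". Under Statistical analysis, the analysis is described as "performed in a blinded manner because analysis of data is done by a special analysis-researcher".
- **Key.** The data are locked before analysis, and the code is broken after it (Randomization and blinding).
- **Identifiers already available.** The allocation envelopes are sealed and sequentially numbered (Randomization and blinding).

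**The concern.** A group letter and a patient number do different work. A patient number says nothing about anyone else. A group letter ties all patients of an arm together, so its protection lasts only until its meaning is known for one of them. Here the letter sits in live clinical records while patients are still being treated and examined, in a trial whose claim to be double blind depends on the physicians and researchers not knowing the arm.

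At stake is the conduct of staff who are meant to be blind. Knowing the arm could affect how questionnaires are explained, how actively adverse events are sought and recorded, which patients an investigator withdraws (Withdrawal from the study allows this), and which patients count as major protocol violators and so leave the per-protocol set (Statistical analysis).

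**Working it through.** **Inputs from the article**

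- Patients: 140 (Abstract, Methods/Design), which agrees with Sample size calculation: 2 × 70 = 140. The 70 per group cannot be reproduced, because the two rates behind it are not printed, but nothing here depends on it.
- Group labels: two, one per arm (Randomization and blinding).
- Needling (Interventions): 10 to 30 mm deep with manual manipulation, repeated with questioning about the sensation every 10 minutes, in one arm; 3 to 5 mm with no manipulation in the other. Participants in both arms have *de qi* explained to them in the same way.
- Physician contact (Secondary outcomes): examinations mid-treatment, at the end of treatment and every 4 weeks of a 12-week follow-up. After randomisation that is 1 + 1 + 12/4 = 5 per patient, or up to 140 × 5 = 700 if nobody drops out.

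**Step 1: what one recognised patient reveals.** The code has two possible readings: A is the *de qi* arm, or B is. One correctly recognised patient settles which. For staff who see the letters of *m* patients:

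- shared letter: *m* arms revealed, at most 140 (that patient and 139 others);
- unique number, no letter: 1 arm revealed.

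**Step 2: is recognition plausible?** Patients know what *de qi* is supposed to feel like, the two procedures feel different, and physicians meet patients repeatedly once treatment has begun. The stated safeguard asks acupuncturists not to discuss procedures and responses with participants or assessors. It does not stop a patient from telling a physician what was done. So recognition is plausible, though the article gives no rate for it.

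**Step 3: illustration.** Assume each patient independently has a chance *q* of being correctly recognised by staff who see all 140 letters. The value of *q* is an assumption and is not in the article. The chance that the code is solved is 1 − (1 − *q*)^140. With unique numbers, the expected count of patients revealed is 140 × *q*.

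| Assumed *q* | Shared letter: chance that all 140 are revealed | Unique number: expected patients revealed |
|---|---|---|
| 0.5% | 1 − 0.995^140 = 50% | 0.7 |
| 1% | 1 − 0.99^140 = 76% | 1.4 |
| 2% | 1 − 0.98^140 = 94% | 2.8 |
| 5% | 1 − 0.95^140 = 99.9% | 7 |

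If the staff concerned saw only half of the records (*m* = 140/2 = 70, also an assumption), then at *q* = 1% the chance is 1 − 0.99^70 = 51%, and 70 arms would be revealed.

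These figures count disclosed labels. They do not measure bias in a treatment effect.

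**The case against.** The best reply is that the chain is conditional. The article does not say who opens the medical records or that outcome assessors use them. Access rules and subject numbering are details that a journal article commonly leaves to the full protocol. The article also keeps the case report forms apart from treatment, to some degree. And VAS, RQLQ and C-MMASS are filled in by patients, whom a staff-side letter does not inform; most other secondary outcomes are laboratory measures; withdrawals are covered by the intention-to-treat analysis.

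Much of this stands. It limits the point to indirect effects and makes it depend on two conditions: sight of the letters and one recognised patient. It does not remove the point, because the letter in the records is a stated rule and not an omitted detail, and examining physicians would ordinarily be expected to use those records.

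A reader might infer more than the article supports:

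- **That needle marks or C-MMASS forms tell physicians the arm.** Nothing says that the two techniques leave different marks, or that C-MMASS passes through the examining physician.
- **That treatment rooms give the arm away.** The article says "Patients in the other treatment group are treated in different rooms". A room identifies an arm only to someone who knows which room serves which arm, and the article does not say that physicians know. The leak would also exist without any letter. Separation may keep patients from observing the other procedure, so mixing rooms is a separate and debatable question.
- **That allocation concealment is weakened.** Earlier letters help to predict the next assignment only under a restricted scheme such as small blocks. No such scheme is stated, and the envelopes are sealed and handled by a separate person.
- **That A/B labels unblind the analyst.** Analysing groups as A and B after lock, with the key opened later, is ordinary masked practice. C-MMASS by group is likely to identify the arms, but that comes from the outcome itself and not from the letter in the medical records.

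**Conclusion.** The point holds in limited form. A group-wide letter in the medical records fits poorly with reserving the allocation for the acupuncturists and with calling physicians and researchers blinded. If staff who see the records correctly recognise one patient, the letter reveals the arm of every patient whose record they see, up to 140, against 1 with a unique number.

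This assumes that the letter is the same for all patients of an arm throughout the trial (the natural reading of the sentence), that staff meant to be blind see it, and that at least one patient is correctly recognised. The article makes the last plausible and does not establish it, so it does not support the conclusion that blinding will fail for all 140 patients, or for physicians, assessors and analyst alike. The size of any resulting bias is unknown. It would act through staff conduct, adverse-event recording, investigator withdrawals and per-protocol decisions, and not through direct scoring of VAS or RQLQ by staff. The weakness is avoidable and worth correcting because the correction is so cheap.

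**What to change.** 1. Remove the A/B letter from the medical records, and from the case report forms if it appears there.
2. Identify patients only by the sequential randomisation (envelope) number.
3. Keep the number-to-arm list with the independent randomisation staff; acupuncturists continue to learn the arm from the envelope.
4. Attach dummy A/B labels to the data set only after database lock, and open the key after the analysis, as now planned.
5. Optionally, finalise the VAS and RQLQ analysis before the analyst sees C-MMASS by group.

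The cost is a change of labelling and of the moment at which group labels are added; step 5 adds only an order of data release. The numbered envelopes already exist, and neither the sample size nor the visit schedule changes. The small downside is that the list must be consulted if a patient's arm has to be known urgently. For patients already enrolled, the letter can be replaced by the number in records still in use, although that cannot undo anything already seen.
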